**Methods and design:**

The Rivastigmine for ECT-induced Cognitive Adverse effects in Late Life depression (RECALL) study combines a multicenter, prospective cohort study on older patients with depression, treated with ECT, with an embedded randomized, placebo-controlled cross-over trial to examine the effect of rivastigmine on inter-ictal delirium. Patients are recruited in four centers across the Netherlands and Belgium. We aim to include 150 patients into the cohort study, in order to be able to subsequently include 30 patients into the trial. Patients are included in the trial when inter-ictal delirium, assessed by the Confusion Assessment method (CAM), or a drop in Mini Mental State Examination (MMSE) score of ≥4 during ECT, develops. In the cohort study, comprehensive measurements of ECT-related cognitive side-effects—and their putative determinants—are done at baseline and during the ECT-course. The primary outcome of the clinical trial is the effectiveness of rivastigmine on inter-ictal delirium-severity, assessed with a change in the Delirium Rating Scale-Revised-98. Secondary outcomes of the clinical trial are several ECT-characteristics and side-effects of rivastigmine.

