### Sample size calculation

We estimated that in our vulnerable study population, prevalence rates of delirium and profound cognitive decline are ~20%, based on a previous study (11). In order to detect a reduction on the DRS-R-98 of 4 points (SD ± 7), at 80% power with α = 0.05, 120 delirious patients should be included in a non-cross-over trial. These patients (*n* = 120) should be identified during regular ECT (cohort study). Since the estimated prevalence of inter-ictal delirium is ~20%, the cohort should include in total at least 600–1,000 persons in order to select 120 patients. This is not possible, due to limited availability of resources. Therefore, a cross-over design will be used. A cross-over design requires fewer patients than a non-cross-over trial to achieve similar power. With an estimated correlation between intra-individual measurements of *r* = 0.50, a cross-over trial requires only 25% of the number of patients (70). Hence, a total of 30 patients provide sufficient power for the trial. With an estimated dropout of 20%, 38 patients need to be included to obtain sufficient power for the trial. We aimed at a probability of 75% to include 38 delirious patients in the trial, which would amount to 210 patients in the cohort. Eventually, with an additional 20% margin of safety due to estimated prevalence, we decided to set the inclusion goal at 250 patients for the cohort, to achieve a sample of 30 delirious patients completing the trial. However, during the first months of data-collection, the prevalence of inter-ictal delirium was noticeably higher, namely ~25%. Hence, in an amendment, the goal of inclusion in the cohort was set back to 150 patients.

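### The amended cohort goal of 150 does not keep the plan's own criterion for reaching 38 trial patients: about 49% at 25% prevalence, against the 75% aimed at, and the abstract states a different trial size

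*Protocol article*

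**What the plan says.** All figures are in the protocol article, mostly under Sample size calculation.

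- Completers: "Hence, a total of 30 patients provide sufficient power for the trial". The Discussion repeats that power rests on 30 patients completing.
- Inclusions: "With an estimated dropout of 20%, 38 patients need to be included to obtain sufficient power for the trial".
- Cohort size, at an assumed prevalence of about 20%: "We aimed at a probability of 75% to include 38 delirious patients in the trial, which would amount to 210 patients in the cohort".
- Margin: "with an additional 20% margin of safety due to estimated prevalence, we decided to set the inclusion goal at 250 patients for the cohort".
- Amendment, after prevalence in the first months looked like about 25%: "Hence, in an amendment, the goal of inclusion in the cohort was set back to 150 patients".

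The abstract (Methods and design) puts the target differently: "We aim to include 150 patients into the cohort study, in order to be able to subsequently include 30 patients into the trial".

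The section on exclusion criteria adds criteria that apply to the trial only: other somatic causes of delirium, and contra-indications to rivastigmine such as bradycardia, AV conduction disorder, current use of a cholinesterase inhibitor or a known reaction to the drug. It gives no figure for the share of delirious patients these remove.

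**The concern.** The text sets a criterion (75% probability of 38 included, plus a margin because prevalence is only an estimate), applies it, then changes one input and presents 150 as the consequence. The new goal sits almost exactly at 38/0.25 = 152, the size at which 38 is merely the expected count. Both the assurance and the margin appear to have gone, and the text does not say so. The 38 and the 75% are neither withdrawn nor restated, so a reader will assume that they still hold.

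The abstract makes the target harder to read. Thirty patients included, with 20% dropout, leaves 30 × 0.8 = 24 completers, not the 30 that the sample size section and the Discussion rely on.

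**Working it through.** **Inputs, all from Sample size calculation:** 30 completers; dropout 20%; 38 included; target probability 75%; prevalence 20% originally and about 25% after amendment; cohort 210, 250, then 150; difference 4, SD 7, correlation 0.50, α = 0.05.

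**Step 1. Reproduce the plan's chain.** Inclusions: 30/0.8 = 37.5, so 38. For the cohort, let X ~ Binomial(N, p) be the number of delirious patients, all assumed to enter.
- P(X ≥ 38 | 210, 0.20) = 0.779. The smallest N reaching 75% is 208 exactly, and 210 by the normal approximation without continuity correction. The stated 210 is reproduced.
- Margin: 210 × 1.2 = 252, stated as 250. P(X ≥ 38 | 250, 0.20) = 0.979.

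**Step 2. Apply the same method to the amended goal.**
- Expected count: 150 × 0.25 = 37.5.
- P(X ≥ 38 | 150, 0.25) = 0.494.
- Smallest N for 75% at 25%: 166 exactly (P = 0.761), or 168 by the approximation that gives exactly 210. With the margin: 166 × 1.2 = 199 or 168 × 1.2 = 202, so about 200.

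**Step 3. Count completers.** If each delirious patient completes with probability 0.8, completers ~ Binomial(N, 0.8p).

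| Cohort | Prevalence | P(≥ 38 included) | P(≥ 30 completers) |
|---|---|---|---|
| 210 | 0.20 | 0.779 | 0.777 |
| 250 | 0.20 | 0.979 | 0.969 |
| 150 | 0.25 | 0.494 | 0.533 |

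**Step 4. Sensitivity of P(X ≥ 38) at N = 150.**
- Prevalence, with full conversion: 0.07 at 20%, 0.38 at 24%, 0.49 at 25%, 0.61 at 26% (0.605 to three places), 0.75 at 27.5%.
- Conversion of delirious patients to trial patients, at 25% prevalence: 0.23 at 90% and 0.07 at 80%. Both shares are assumptions, since the article gives none.

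**Step 5. Separate the count from power.** The SD of the within-patient difference is 7 × √(2 × (1 − 0.50)) = 7. For a two-sided paired t-test at 0.05 with n completers, the noncentrality is 4√n/7.

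| Completers | Power |
|---|---|
| 24 | about 76% |
| 26 | about 80% (0.7996, just under) |
| 27 | about 82% |
| 30 | about 86% |

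At N = 150, prevalence 25%, full conversion and 20% dropout, completers ~ Binomial(150, 0.20). So P(≥ 27 completers) = 0.76, and power averaged over that distribution is about 85%. In terms of inclusions, 27/0.8 = 33.75, so 34, and P(X ≥ 34 | 150, 0.25) = 0.773.

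**The case against.** **The 75% was stated for 210, in the past tense, and no probability is attached to 150.** This is true. The article never says that 150 gives 75%. But the requirement of 38 included and 30 completing is still the current text, the Discussion repeats the 30, and the amendment is offered as the consequence of a change in prevalence alone. If the criterion was dropped, the text should say so.

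**The article condenses a fuller protocol, and the amendment may hold the reasoning.** A missing calculation for 150 would be weak ground by itself. The point is different: the article sets out the full chain and ends on a number that the chain does not yield.

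**The 25% is approximate, so a bare 49% is too precise.** This stands. The probability moves from 0.38 to 0.61 between 24% and 26%, and prevalence of 27.5% would restore 75%. So 49% is the value at 25%, not an upper bound. The 20% prevalence and the 80% and 90% conversion figures are sensitivity cases only.

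**The target may now be 30 included, as in the abstract.** P(X ≥ 30 | 150, 0.25) = 0.937, but that leaves about 24 expected completers from 30 included, against the 30 required elsewhere.

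**A reader might infer that the trial has only an even chance of adequate power.** The documents do not support that. On the plan's own difference, SD and correlation, 27 completers give just over 80% power, and 150 yields at least that many with probability about 0.76 at 25% prevalence and full conversion. A reader might also infer that the cohort must be enlarged or recruitment tied to the number randomised. Nothing in the text makes that necessary: 150 is called a goal, and the article cites limited resources and feasibility.

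**Conclusion.** The point holds as an error in the stated recruitment figures. By the method that reproduces 210 and 250, the amended 150 gives about 49% for 38 included and 53% for 30 completing, with no margin. Keeping the 75% would take 166, or about 200 with the margin. This assumes 25% prevalence, independent patients, 20% dropout and every delirious patient entering the trial. The trial-only exclusions would lower the figures by an amount that cannot be computed from the article.

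The consequence for power is milder. At 25% prevalence and full conversion, 150 meets an 80% power aim with roughly the assurance first sought. That reassurance depends on both conditions. At an assumed 80% conversion the expected completers are 150 × 0.25 × 0.8 × 0.8 = 24, which corresponds to about 76% power.

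The abstract's 30 included contradicts the 38 included and 30 completing of the sample size section, whichever way the first matter is settled.

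**What to change.** In Sample size calculation, do one of the following.

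1. Keep 38 included and state that 150 gives about 49%, not 75%, at 25% prevalence and full conversion, with no margin. Add expected completers (150 × prevalence × conversion × 0.8) over a range:

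| Prevalence | 100% conversion | 90% | 80% | 70% |
|---|---|---|---|---|
| 25% | 30 | 27 | 24 | 21 |
| 20% | 24 | 21.6 | 19.2 | 16.8 |

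2. Restate the requirement as about 34 included for 27 completers, show the power calculation behind it, and state that 150 gives about 77% at 25% prevalence and full conversion.

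Under option 1, correct the abstract to 38 included and 30 completing, in agreement with the sample size section and the Discussion. Under option 2, carry the restated numbers through all three places.

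The cost is a few sentences. No patients are added and the recruitment stopping rule need not change. Under option 1 the stated assurance simply becomes less favourable.

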### Data collection, management, and analysis

#### Data collection and retention

All assessors are trained in the questionnaires or instruments they assess. In addition, they are trained to motivate patients to complete follow-up. All training sessions for the Recall study are recorded in a training log.

#### Data management

The acquired data and examination results will be entered into an electronic case record form (eCRF), stored on a laptop, only accessible by members of the research team. Where it is necessary to be able to trace data to an individual subject, a subject identification code list will be used to link the data to the subject. This code list will be stored at the department of psychiatry Amsterdam University Medical Center—location VUmc. The key to the code will be safeguarded by the data management in case the data or the blood samples are kept for a longer period of time. The handling of personal data is in accordance with the Dutch Personal Data Protection Act (in Dutch: De Wet Bescherming Persoonsgegevens).

#### Data analysis

Significance will be set at *p* < 0.05 for all statistics and 95% confidence intervals will be presented. Intention to treat analyses will be conducted. Descriptive baseline statistics will be generated for the patients included in the trial. As the trial is a patient cross-over design, no comparison or correction for baseline variables will be done.

To estimate the efficacy of rivastigmine on inter-ictal delirium in the RECALL trial, delta scores of the DRS-R-98 will be used. These delta scores will be computed over the period of rivastigmine (intervention, 2 ECT sessions, 7 days) and placebo (comparison, 2 ECT sessions, 7 days) separately. For further details, see section Primary outcome measure. Analysis of Variance (ANOVA) by a mixed model for repeated measures, with treatment (rivastigmine vs. placebo) as a within effect and sequence of treatment (arm A vs. arm B) as a between factor, will be performed. Additionally, the association between rivastigmine and (delta-scores of the) DRS-R-98 will be examined in a traditional regression model, with putative effect modifiers, confounders and determinants.

Cox's regression analyses will be conducted in the RECALL cohort, with outcome defined as the (time to) occurrence of inter-ictal delirium measured by a positive CAM and/or a decline of MMSE of 4 points, adjusted for putative effect modifiers, confounders and determinants. Additionally, putative patterns of cognitive decline will be identified by data-driven methods (e.g., latent-class analysis), based on cognitive outcome measures. Future analyses in the data will depend on appropriate research questions.

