### Study population and inclusion criteria

In- and outpatients, aged 55 years or older, fulfilling the Composite International Diagnostic Interview CIDI) criteria of a Major Depressive Episode—in the context of a unipolar major depressive disorder or bipolar disorder- and referred for ECT-treatment, are asked to participate in the cohort and, in case of occurrence of inter-ictal delirium, in the trial (22–24). Before inclusion, they provide a written informed consent form. The presence of an inter-ictal delirium is examined with the Confusion Assessment Method (25) (CAM) and/or Mini Mental State Examination (26) (MMSE), administered by a trained research assistant. For a diagnosis of inter-ictal delirium, patients need to have a CAM score indicating delirium or a drop in MMSE-score of at least 4 points as compared to baseline. The evaluation of inter-ictal delirium was done during regular screening once weekly, preferably in the middle of a week, 1 day (and maximum 2 days) after ECT. This timing was chosen to (1) select persistent cases of delirium, and hence not to include mild disorientation or transient delirious episodes immediately post-ECT; (2) to increase feasibility by avoiding cognitive testing during weekends and (3) to diminish the learning effect of repeated cognitive testing. Once delirium was diagnosed, an evaluation was done by the clinician to indicate whether it was needed to further exclude possible causes of delirium.

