### RECALL trial: Treatment allocation, intervention, and blinding

After inclusion in the trial, randomization is organized with a two by two Williams design (29). Block randomization is performed by the pharmacy department of the Amsterdam University Medical Center—location VUmc, with stratification for each site. Patients are randomly assigned to either the rivastigmine-followed-by-placebo group, or the placebo-followed-by-rivastigmine group. Each treatment arm lasts for four consecutive ECT sessions (Figure 1). Except for the unblinded nurse or research assistant (i.e., nurse or research assistant who is not involved in other parts of the study, nor in clinical practice, but only applies the patches), all other study members are blinded. “Trial treatment randomization lists” with codes are provided by an independent pharmacist and will only be available for the unblinded nurse or research assistant who applies the patches. Rivastigmine patches delivering 4.6 mg/24 h (Hexal AG, Holzkirchen, Germany) and Hansaplast® placebo patches (of similar size) are labeled in accordance with EU GMP annex 13 regulations and supplied to the sites. To improve and monitor adherence to the trial protocol, drug accountability lists are filled in. The Tmax of rivastigmine patches is 10–16 h, therefore the application of the rivastigmine (and placebo) patches is done the evening prior to ECT. The patch is removed after 24 h. As previously mentioned, during the trial, co-medication is allowed and there are no restrictions to clinical care as usual. As specified in the exclusion criteria however, patients with adjustments in antipsychotic medication or in electrode placement, are excluded from the trial. Benzodiazepines are allowed (e.g., in cases of profound agitation or insomnia). All changes in medications during the trial are registered after every ECT-session. Prior to each ECT-session, side-effects of rivastigmine are assessed, and in case of serious side-effects (e.g., gastrointestinal adverse reactions such as severe nausea), the participation in the trial will be stopped and rivastigmine discontinued. In case of persistent side-effect after discontinuation, the clinician will treat the patient according to the clinical picture (e.g., anti-emetics in case of nausea).

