### Outcome measures

Table 1 shows a full summary of patient characteristics and outcome measures, including the time of collection.

**Table 1 T1:** Collection of patient characteristics and outcome measures in the RECALL trial and cohort.

	**Baseline**	**Regular care**		**Trial**							**Regular care in cohort**		
		**in cohort**									**after finishing the trial**		
	**Baseline**	**Max 90 minutes after ECT**	**Once a week during ECT** ^∧^	**Day before first ECT**	**Max 90 minutes after first ECT**	**Max 90 minutes after 2**^nd^ **ECT**	**Day after 2**^nd^ **ECT**^∧^	**Max 90 minutes after 3**^rd^ **ECT**	**Max 90 minutes after 4**^th^ **ECT**	**Day after 4**^th^ **ECT**^∧^	**Max 90 minutes after ECT**	**Once a week during ECT** ^∧^	**1 week after stop ECT**
Time	Ta	Tb		T0	T1	T2	T3	T4	T5	T6	Tb		
Socio-demographics	X												
*General clinical-demographics*													
Medical history	X												
Substance use	X												
Medication use	X	X		X	X	X		X	X	X	X		X
ATHF	X												
BMI	X												
Waist circumference	X												
Blood pressure	X												
*Physical activity and frailty*													
Frailty index	X												X
SPPB	X												X
Physical activity*	X												
Vision and hearing ability	X												
*Depression related clinical characteristics*													
BAI^a^	X												
GDS^a^	X												
AES^a^	X			X			X			X			X
MADRS^a^	X		X				X			X		X	X
CORE	X		X				X			X		X	X
*Neurocognitive characteristics*													
Battery of neuropsychological tests**	X												X
Self reported cognitive decline	X												X
IQCODE	X												X
(f)MRI	X												
EEG	X												
*Laboratory characteristics*													
Blood / urine sample	X			X									X
*Primary outcome measure*													
DRS-R-98				X	X	X	X	X	X	X			
*Secondary outcome measures*													
MMSE	X		X				X			X		X	X
Letter fluency	X			X			X			X			X
Clock Drawing Test	X			X			X			X			X
Reorientation time		X			X	X		X	X		X		
RASS		X			X	X		X	X		X		
CAM		X	X										
ECT characteristics		X			X	X		X	X		X		
Rivastigmine side-effects				X	X	X		X	X	X			

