#### Primary outcome measure

During the trial, the effect of rivastigmine on inter-ictal delirium is examined through the Delirium Rating Scale-Revised-98 (DRS-R-98) (30). It was demonstrated that the DRS-R-98 is sensitive, specific, reliable, and easy to use for the assessment of severity of a delirium (30). We will compare delta-scores of the DRS-R-98 computed over the period of rivastigmine-use and placebo (T3-T0 and T6-T3, depending on whether the patients start with rivastigmine or placebo). This is assessed by a trained, blinded research nurse once weekly.

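### The primary cross-over model names treatment and sequence but not period, although the two delta scores are not measured on a like-for-like basis

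*Protocol article*

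**What the plan says.** All references are to the protocol article.

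- **Design.** Under treatment allocation, "randomization is organized with a two by two Williams design", in blocks, "with stratification for each site". There are two sequences and two periods.
- **Outcome.** Under Primary outcome measure, each patient yields two DRS-R-98 changes: "T3-T0 and T6-T3, depending on whether the patients start with rivastigmine or placebo". Both use T3.
- **Primary model.** Under Data analysis the method is named as "Analysis of Variance (ANOVA) by a mixed model for repeated measures". The terms that the section then gives for this model are these two: "with treatment (rivastigmine vs. placebo) as a within effect and sequence of treatment (arm A vs. arm B) as a between factor". No other term is listed. Period is mentioned neither there nor in the Discussion, which treats carry-over as the potential cross-over bias.
- **Additional analysis.** In the same section, the association of rivastigmine with the DRS-R-98 and its delta scores "will be examined in a traditional regression model, with putative effect modifiers, confounders and determinants". How a patient's two values are handled is not stated.
- **Timing.** In Table 1, T0 stands under "Day before first ECT", whereas T3 and T6 stand under the day after the second and the fourth ECT. Eligibility screening, by CAM and/or MMSE, takes place "preferably in the middle of a week, 1 day (and maximum 2 days) after ECT".

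**The concern.** In a two-period cross-over, the within-patient treatment contrast has opposite signs in the two sequences with respect to period. If the period difference is not fitted, it appears as extra scatter between the sequences' contrasts and enters the error term. If the sequences are unequal in size, part of it also enters the treatment estimate.

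There are three reasons to expect a period difference here.

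- Patients are selected on a positive screen shortly after an ECT, so some fall back towards their usual level is likely in period 1.
- T3-T0 compares a rating the day after an ECT with one the day before an ECT, whereas T6-T3 compares two day-after ratings. The first delta therefore contains a change in time since ECT that the second does not.
- The ECT course continues through both periods.

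The first two may act in opposite directions. Regression to the mean lowers T3 relative to T0, while rating closer to an ECT may raise it. The net size and sign are unknown, which is a reason to estimate the term.

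The additional regression raises a related matter. Two deltas that share T3 with opposite signs are unlikely to be independent.

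**Working it through.** **The plan's own figure.** The Sample size section gives a 4-point effect, SD 7, r = 0.50 and 120 patients for a parallel design, and needs 25% of that for the cross-over. The reduction reproduces: 120 × (1 − 0.5)/2 = 30, and 30/0.8 = 37.5, i.e. 38. The starting 120 does not: two-sided 5% and 80% power give 49 per arm, 98 in total. This does not affect the present point, which takes 30 completers as given.

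**Period and interaction are one term.** Code sequence, treatment and period as ±1 in the four cells of the design. Treatment × sequence then equals period up to sign. Adding period to intercept, sequence, treatment and interaction leaves the rank of the design matrix at 4. A model with the interaction has therefore removed period, and a main-effects model has not.

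**Power, with r = 0.5 on raw scores.** Assumptions not in the documents: the three ratings are equally correlated; the 4-point effect acts on the raw score at the end of the rivastigmine period and is gone after placebo; sequences are 15:15; T3 and T6 lie 4 points below T0 whatever the treatment.

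- Delta variance: 2 × 49 × (1 − 0.5) = 49. Covariance of the two deltas: −49 × (1 − 0.5) = −24.5, a correlation of −0.5.
- Variance of the rivastigmine-minus-placebo difference of deltas: 49 + 49 + 2 × 24.5 = 147.
- Expected difference from treatment alone: rivastigmine first, −4 − 4 = −8; placebo first, −4 − 0 = −4. Mean −6.
- The fall of 4 in T3-T0 moves these to −12 and 0. The mean is still −6, with each sequence 6 away from it.
- Period fitted: SE = √(147/30) = 2.21, 28 df, power about 75%.
- Period omitted: error variance 147 + 36 × 30/29 = 184, SE = √(184/30) = 2.48, power about 67%.
- With a 6-point fall, power is about 60% without period and 75% with it.
- With no treatment effect and the 4-point fall, the model without period rejects in about 4% of trials, not 5%.

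Powers and rejection rates are from simulation, at least 20,000 trials per setting. The sign of the shift matters on this scale. A 4-point rise gives −8 + 4 = −4 and −4 − 4 = −8, each only 2 from the mean, the same spread as with no shift, so almost nothing is lost.

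**Power, with r = 0.5 on the deltas.** The documents do not say which quantity r describes. On this reading the SD of the difference is 7 × √(2 × 0.5) = 7 and SE = 7/√30 = 1.28. Omitting a 4-point period effect multiplies the SE by √(1 + 16/49) = 1.15. Power falls from 86% to 77%, and type I error from 5% to 2.5%. The direction is the same.

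**Bias with unequal sequences.** With period omitted, the estimate averages over all completers. With no treatment effect, a 4-point fall and a 17/13 split, it is (17 × (−4) + 13 × 4)/30 = −0.53 points. With period fitted, the bias is zero.

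**Additional regression, if rows are treated as independent.** For correlation ρ between a patient's deltas, the true treatment SE is √(1 − ρ) times the reported one, so type I error is about 2 × [1 − Φ(1.96/√(1 − ρ))].

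| Assumption | ρ between deltas | Type I error |
|---|---|---|
| Raw scores equally correlated | −0.50 | 11% |
| Raw scores AR(1), 0.5 | −(1 − 0.5)/2 = −0.25 | 8% |
| Raw scores AR(1), 0.8 | −(1 − 0.8)/2 = −0.10 | 6% |
| r = 0.50 applies to the deltas | +0.50 | below 1% |

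For covariates that vary only between patients the error runs the other way: standard errors are too wide when ρ is negative and too narrow when it is positive.

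**The case against.** The description of a within effect and a between factor is the language of a classical ANOVA that ordinarily includes their interaction. If it is fitted, period is already removed and the standard error is right. A journal article may also leave the full term list to another document. This stands as far as it goes: a reader might infer that the primary standard errors are wrong, and the text does not establish that. But the section does list its terms, the interaction is not among them, and the two readings are different models with different power.

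Even under the main-effects reading, the primary analysis does not gain false positives when sequences are balanced. It becomes conservative, and with no period effect nothing changes. Blocked, site-stratified randomisation works towards balance. All of this stands. Bias needs unequal completers, which the expected 20% dropout could produce but need not.

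The period shift has no value in the documents. Screening was timed to select persistent cases, and entry rests on CAM or MMSE rather than the DRS-R-98, so regression to the mean may be modest. A reader should not infer that patients enter at a peak of confusion. The difference in timing between T0 and T3/T6 is on the face of Table 1, but its effect is unmeasured.

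For the additional regression, a reader might infer from the word traditional that pairing is ignored and that intervals are too narrow. The article does not say that rows are treated as independent, and the direction of any error depends on a correlation it does not give. Nor does it name a random patient intercept, so faults specific to that model cannot be charged to the plan.

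**Conclusion.** The point holds in a limited form. As written, the primary model does not secure adjustment for period, in a trial whose two deltas differ by design in time since ECT. If only the named main effects are fitted, the likely cost is power, illustrated by 75% to 67%, with a bias of about 0.5 points if completers split 17/13. Both figures rest on an assumed 4-point fall after T0, SD 7 and 30 completers; the power figure also rests on r = 0.5 on raw scores. A different size or sign of shift changes them, and the loss may be negligible.

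The documents do not support saying that the error estimates are wrong in both analyses, or that the primary test exceeds its 5% level. The point about the regression is secondary and conditional: type I error of about 6% to 11% if rows are treated as independent and the deltas are negatively correlated, which the shared T3 makes plausible, and conservative for treatment if the correlation is positive.

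**What to change.** State in the primary model that period is a fixed effect alongside treatment and sequence, with the two values of a patient modelled as correlated. Naming the treatment-by-sequence interaction is equivalent, but period is clearer.

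For the additional regression, state one of the following: fit it on each patient's within-patient difference, use standard errors clustered on patient, or use a 2 × 2 covariance that allows negative correlation.

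The cost is one degree of freedom in the primary model and a few words in the analysis text, best settled before unblinding. Sample size, visits and data collection do not change.
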